#### Treatment as usual

All 60 participants will continue receiving treatment as usual; the study does not affect concomitant interventions in any way. However, we will measure service use, so all current treatments for all patients are recorded. TAU is not expected to affect the outcome measures or systematically differ between participants, but intensity of current treatments is stratified between intervention arms.

#### CRT intervention

CRT will be delivered over the course of a 12-week period, flexibly utilising a combination of formats (i.e., face-to-face, telephone, drop-in sessions and individual practice), amounting to approximately 30–40 hours of CRT. Face-to-face sessions (up to 1 hour long) will be held at least once per week, but participants will be encouraged to attend up to three sessions per week if feasible; an alternative arrangement of twice-weekly telephone sessions (in addition to one face-to-face session) will be offered. Additionally, all individuals will be provided unlimited access to use the program in their own time, for practising independently as they wish, with an option to receive reminder text-messages that can be sent to participants up to twice per week. This intervention aims are tailored to individual needs, using a format beneficial for themselves specifically. Where possible, and only with the participants’ agreement at each session, therapy meetings will be video-recorded or auditory-only recorded; this will assist with ensuring therapist fidelity and optimising the intervention for future use. CRT is considered a safe therapy, unlikely to have an impact on risky behaviours, and the participants should not be experiencing symptoms during the trial. Though we perceive this not to be a high-risk study, the participants are considered a vulnerable population, and a small risk exists that they will not engage positively with, or more importantly, will have a negative emotional reaction to the intervention (e.g. frustration may be experienced upon failure to complete a particular task). Despite existing evidence indicating that people find CRT helpful and acceptable, we will ensure that CRT therapists are comprehensively trained and prepared to manage such situations (using supportive and solution-focused approaches). Effort will be put into avoiding such circumstances by following standardised protocols which researchers will be trained in for adverse situations. We emphasise that the intervention is delivered using positive methods and has reliably elicited positive feedback from patients during previous trials. CRT therapists will be psychologists (to post-graduate-level study at minimum), who have received specific training from experts in the intervention, on CRT and the CIRCuiTs program specifically. They receive ongoing supervision from experienced CRT practitioners. Processes are in place to deal with any safety issues that include ongoing participant monitoring throughout the intervention period; completion of self-report symptom measures on a monthly basis, and prompts from a researcher to safeguard completion and scoring. In any instances where scores exceed the standardised cut-offs for depression or mania, individuals will receive a call from a researcher (or a therapist if concerns persist). If necessary, a therapist or clinician and participants will discuss and agree whether there is a need for trial withdrawal. Additional concerns about safety and wellbeing will be conveyed to the participant’s contact healthcare professional. A copy of the consent form alongside a letter of notification and information sheet is sent to nominated healthcare professional for all participants. Trial participation (and whether CRT is being undertaken) is to be recorded on patient’s health records as the trial affects clinical care and may be important for treatment-related decisions. A data management plan (in adherence with the Research Governance Framework) has been developed to ensure protocols for quality assured monitoring and safety are maintained during the trial. Data monitoring support is also accessible through the trial steering committee and trial specific working manual.

### Measures

See Table 1 for a summary of study measures at each time point.

**Table 1 Tab1:** Study measures and time points

Concept	Measure	Screen A	Screen B	Week 0	Week 1	Week 4	Week 8	Week 12	Week 13	Week 25
Cognitive	Wechsler Adult Intelligence Scale (WAIS)			X					X	X
	Wechsler Abbreviated Scale of Intelligence (WASI)			X					X	X
	Wechsler Memory Scale (WMS)			X					X	X
	Delis-Kaplan Executive Function System (DKEFS)			X					X	X
	Hotel Test			X					X	X
	Test of Premorbid Functioning (TOPF)			X						
	Perceived Deficits Questionnaire (PDQ)			X					X	X
Functional	Functional Assessment Short Test (FAST)			X					X	X
	Goal-attainment Scale (GAS)			X					X	X
Mood-related	Toronto Alexithymia Scale (TAS-20)			X					X	X
	Hamilton Rating Scale for Depression (HAMD)	X	X	X					X	X
	Young Mania Rating Scale (YMRS)	X	X	X					X	X
	Inventory of Depressive Symptomatology (IDS)	X	X	X	X	X	X	X	X	X
	Altman Self-rating Mania scale (ASRM)	X	X	X	X	X	X	X	X	X
	Hamilton Anxiety Rating Scale (HAM-A)			X						
Psycho-social	Childhood Trauma Questionnaire (CTQ)			X						
	Structured Clinical Interview for DSM (axisII), BPD scale (SCID-BPD)			X						
	Standardised Assessment of Personality – Abbreviated Scale (SAPAS)			X						
	Trait Self-description Inventory (TSDI) of personality			X						
Other	Qualitative questions			X					X	
	Client Service Receipt Inventory (CSRI)		X						X	X
	WHO quality of life measure (EQ-5D)		X						X	X
	Mini Neuropsychiatric Interview (MINI)	X								
	Montreal Cognitive Assessment; (MoCA)	X								
	Demographic information			X					X	X

Week 0 = baseline assessment, Week 13 = post-intervention assessment, Week 25 = follow-up assessment

In addition, at the three main assessment time points (weeks 0, 13 and 25), the additional outcomes are measured: The Functional Assessment Short Test (FAST [29]) calculates everyday functioning; the Goal Attainment Scale (GAS), a personalised measure of goal attainment [30]; and experiences of alexithymia (assessed using the Toronto Alexithymia Scale; TAS-20 [31]. Researcher-rated severity of depressive (Hamilton Rating Scale for Depression; HAMD [32]) and manic (Young Mania Rating Scale; YMRS [33]) symptoms are conducted to establish euthymia at screening (both A and B) and at the three assessment time points (weeks 0, 13 and 25). Subjective symptom assessments are additionally conducted at all study time points (0, 1, 4, 8, 12, 13 and 25 weeks) using the Inventory of Depressive Symptoms (IDS [34]) and Altman Self-Rated Mania (ASRM [35]) scales.

Before (week 0) and after the intervention (week 13), qualitative questionnaires will measure the feasibility and satisfaction with Cognitive Remediation Therapy [36].

Extent of current health service-usage and health-related quality of life are assessed using an adapted version of the Client Service Receipt Inventory (CSRI [37]) and the EQ-5D measure [38]) respectively, at the second screening session (Screen B) and then after treatment (week 13) and follow-up (week 25). These measures are used also to calculate the estimated cost of providing CRT (alongside data recorded from CRT, e.g. number of therapist hours).

Attendance to face-to-face and telephone sessions, as well as amount of time spent individually practising CRT will be monitored; the CIRCuiTs program records extensive data regarding usage automatically.

#### Secondary outcomes

Approximate premorbid IQ is measured using the Test of Premorbid Function (TOPF [39]) at baseline (week 0). Also at the baseline assessment only (week 0), anxiety levels are measured using the Hamilton Anxiety rating scale (HAM-A [40]), history of childhood trauma using the Childhood Trauma Questionnaire (CTQ [41]), personality disorder traits (using the SCID-BPD; Structured Clinical Interview for DSM-IV disorders, borderline scale [42] and SAPAS; the Standardised Assessment of Personality–Abbreviated Scale [43]) and general personality traits (assessed using the TDSI; The Trait Self-Description Inventory [44]).

#### Other measures

At Screen A, the diagnostic assessment includes the MINI (Mini International Neuropsychiatric Interview [16] structured assessment for common mental disorders; the bipolar disorder, substance use, and personality disorder sections to be completed first to determine eligibility, and the MoCA (Montreal Cognitive Assessment [45]) which screens for symptoms of dementia (for inclusion total score must be below 26). Demographic information collected (at Screen A and week 0) includes data regarding age, employment, physical health and recent life events. All regular medications of each participant will be recorded and any changes in medication will be noted at the post-intervention and 12-week follow-up sessions. We will carefully monitor adverse events and patient safety at every time point (Weeks 0, 1, 4, 8, 12, 13 and 25), and any concerns in this regard will be promptly taken to the Lead PI and Steering Committee.

### Statistics

Analyses will be carried out by the trial statistician. The main purpose of the statistical analyses is to estimate trial and intervention feasibility parameters. Thus, we will use largely descriptive statistics with inferential statistics used to generate respective confidence intervals and effect sizes. The analyses can be split into three aims: 1) estimation of parameters that evaluate trial feasibility (recruitment rates, randomisation rates and attrition rates), to meet objective 4; 2) estimation of parameters that measure intervention feasibility (adherence, treatment fidelity and patient satisfaction) in accordance with objective 3; and 3) estimates of intervention effect sizes (mean differences and standard deviations) in terms of potential primary outcomes of future trials or variables that are targeted by the therapy (putative mediators of future treatment effects), addressing objectives 1 and 2. All statistical analyses will adopt the intention-to-treat (ITT) principle and will be conducted after data collection has been completed.

#### Trial feasibility (objective 4) and intervention feasibility (objective 3) parameters

The analysis will firstly consist of descriptive statistics to assess the rate of consent of eligible patients, the acceptability of CRT to the patient population, treatment fidelity, deviations from study protocol and study retention. Participant demographic and clinical characteristics will also be summarised at baseline. Patterns of missing data or nonattendance will be described for the outcome at measurement time-points and according to therapy session, along with reasons for drop-out. As appropriate, the statistics derived will be means and standard deviations or medians, minimum values, maximum values and interquartile range for continuous measures and proportions for ordinal or multinomial categorical measures and binary coded measures.

#### Estimates for effect sizes for CRT versus TAU (objectives 1 and 2)

To assess improvement in cognitive and functioning domains, estimates of treatment effect sizes will be obtained using linear mixed models. These analyses will provide the treatment effect estimate on each outcome at 13 and 25 weeks. The linear mixed model will contain post-treatment measures of the outcome at the two follow-up time points, i.e. 13 and 25 weeks as the dependent variables with fixed effects of trial arm, baseline measure of outcome, time and a time point by trial arm interaction to allow treatment effects to differ at 13 and 25 weeks. Baseline measures of the primary outcomes are included as they are potential predictors of future outcome and thus should help us to gain precision for effect estimates of interest. A random effect for participant will be entered in to the model to account for correlations between the two repeated measures per participant. In addition, to account for the correlation of level-1 residuals across time, an exchangeable residual covariance structure will be included in the model. We will also consider changes in cognitive variables as mediators of improvements in functional outcomes (FAST). The aim here is to derive an effect size and inferential statistics will not be reported.

With respect to missing data, linear mixed models will be estimated using maximum likelihood (ML). Such an approach provides valid inferences under the assumption that the missing data mechanism is ignorable (or missing at random, MAR). Here, this means that explanatory variables included in the model can predict missingness as can earlier observed values of the outcome. We will include baseline predictors of drop-out as explanatory variables in the linear mixed model to make the MAR assumption more realistic. However, given the small dataset the number of explanatory variables to be included will be necessarily small. Finally, Sensitivity analysis will be used to assess the robustness of the conclusions to missing outcome data in which missing values will be imputed according to various plausible scenarios, e.g. participants with missing data showing no improvement in cognitive outcomes.

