### Objectives

The overarching aim of this trial is to determine whether CRT can serve as a new, evidence-based treatment for bipolar disorder. In order to achieve this, the following research questions are being investigated as primary objectives, as they are all fundamental pre-requisites of future examination of CRT for bipolar disorder:Does CRT improve overall cognition (specifically learning, verbal and working memory, intellectual functioning, attention and executive functions)?Does CRT provide further, specific benefits to participants (i.e. everyday functioning, mood symptoms and achievement of self-defined goals)?Do people with bipolar disorder feel that CRT is beneficial and acceptable?Can sufficient patients be recruited to conduct a larger, more comprehensive RCT?

Potential moderators or mediators for the benefits of CRT will additionally be explored on a secondary basis.

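### The mediation effect size is to be reported without inferential statistics, which read literally leaves the indirect effect with no confidence interval, contrary to the plan's own general rule

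*Protocol article*

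**What the plan says.** Three places in the protocol article bear on this.

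- **Statistics, opening paragraph.** The general rule is: "we will use largely descriptive statistics with inferential statistics used to generate respective confidence intervals and effect sizes". In this sentence, inferential statistics are the means by which intervals are obtained. The third aim then lists effect-size estimates for possible outcomes of future trials or for "variables that are targeted by the therapy (putative mediators of future treatment effects), addressing objectives 1 and 2".
- **Estimates for effect sizes for CRT versus TAU (objectives 1 and 2).** After setting out the linear mixed model for weeks 13 and 25, the first paragraph adds that changes in cognitive variables will be considered as mediators of improvement in FAST. It closes with: "The aim here is to derive an effect size and inferential statistics will not be reported".
- **Objectives.** The status of this work is given as: "Potential moderators or mediators for the benefits of CRT will additionally be explored on a secondary basis".

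**The concern.** The closing sentence is a stated reporting rule, not a detail left open for a fuller document. An analysis plan that followed it would carry it forward. It uses the same term as the opening of the Statistics section but points the other way: there, inferential statistics supply intervals; here, they are withheld.

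An indirect effect is the product of two estimated coefficients, each of them noisy with 60 participants. Given only the product, a reader cannot tell how precise it is, or whether the data are compatible with no mediation or with an effect of the opposite sign. The Statistics section makes estimation the purpose of the trial, so precision is the part of the result that matters most.

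There is also a question of scope. The word *here* most naturally points to the mediation sentence just before it. Because it closes the paragraph that defines the main models, it could also be taken to cover the CRT versus TAU effects themselves. That would widen the conflict with the general rule.

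**Working it through.** **Step 1: the texts side by side.** General rule: inferential statistics generate confidence intervals and effect sizes. Mediation sentence: an effect size, without inferential statistics. Taking the term in the document's own sense, what drops out for mediation is the interval.

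**Step 2: inputs for the size of the problem.** The article states no power, alpha, effect size or SD, so there is no figure of its own to reproduce.

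- n = 30 per arm (Participants; Trial design).
- *a*, the CRT effect on the mediator: 0.3 or 0.5 SD. Assumed.
- *b*, the mediator-outcome slope given arm: 0.2, 0.3 or 0.4. Assumed.
- Mediator residual SD 1, outcome residual variance 1 − b², no direct effect, complete data. Assumed.

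**Step 3: hand calculation for a = 0.5, b = 0.3.**

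- SE(a) = √(2/30) = 0.258.
- SE(b) ≈ √[(1 − 0.09)/56] = 0.127. The 56 is the 58 within-arm degrees of freedom less 2, from the mean of an inverse chi-square.
- SD(ab) = √[a²·SE(b)² + b²·SE(a)² + SE(a)²·SE(b)²] = √[0.00406 + 0.00600 + 0.00108] = √0.01115 = 0.106, against a true value of 0.15.

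**Step 4: simulation.** The estimate is the product of the two coefficients, with 4,000 simulated trials per setting at 30 per arm. The last column is the chance of an estimate below zero, computed directly as P(a<0)·P(b>0) + P(a>0)·P(b<0) from normal approximations with the standard errors above.

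| a | b | True ab | Sampling SD | Central 95% of estimates | Chance of wrong sign |
|---|---|---|---|---|---|
| 0.3 | 0.2 | 0.06 | 0.074 | −0.050 to 0.233 | 17.0% |
| 0.3 | 0.3 | 0.09 | 0.092 | −0.064 to 0.299 | 13.0% |
| 0.3 | 0.4 | 0.12 | 0.113 | −0.078 to 0.359 | 12.3% |
| 0.5 | 0.2 | 0.10 | 0.089 | −0.030 to 0.311 | 8.6% |
| 0.5 | 0.3 | 0.15 | 0.106 | −0.009 to 0.395 | 3.5% |
| 0.5 | 0.4 | 0.20 | 0.124 | −0.012 to 0.468 | 2.7% |

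A separate run of 400 trials at three of these settings gave SDs of 0.078, 0.107 and 0.126. The sampling SD is therefore about 0.07 to 0.13. Zero lies inside the central 95% in all six settings, but only just in the last two: a wrong-sign chance above 2.5% is what puts it inside, and 2.7% barely does. With an assumed 24 per arm after drop-out, the SDs rise to between 0.085 and 0.139.

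**Step 5: what the wider reading would remove.** For a standardised difference between arms, unadjusted for baseline, the 95% half-width is 1.96 × √(2/30) = 0.51 SD. If the sentence covered the main effects too, uncertainty of that order would go unreported. Baseline adjustment should narrow it somewhat.

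**The case against.** The strongest reply is that the sentence is a deliberate exception. The general rule speaks of largely descriptive statistics, mediation is secondary, and no progression rule or primary conclusion rests on it. The authors may also have meant only that no hypothesis tests would be reported, which is close to the fix proposed here. Part of this stands: it lowers the severity and justifies leaving out p-values. It does not justify leaving out precision. If only p-values were meant, the sentence still needs rewording, because the Statistics section uses the term for what produces intervals.

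It can also be said that the third aim concerns differences between arms on the putative mediators, not indirect effects. That is correct. The conflict is with the general sentence on intervals, not with that list.

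The magnitude depends on assumed paths, and the spread of estimates across simulated trials is not the interval one trial would report. Both points stand. The Limitations section also already concedes that the sample is relatively small.

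Stronger readings are tempting but not supported:

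- A reader might infer that mediator and outcome will be taken at the same visit, so that direction cannot be established. The article names no visits for the mediation analysis. Table 1 schedules both cognition and FAST at weeks 0, 13 and 25, so an ordered analysis is open, and a condensed article may leave this to a fuller document.
- A reader might infer that the estimate would be uninterpretable. It would lack a measure of precision, which is less than that.
- A reader might infer that the indirect effect is meant to select targets for the larger trial. The Limitations section says only that the results in general will inform a further RCT.

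**Conclusion.** The point holds in a narrow form and at low severity. As written, the mediation sentence withholds confidence intervals from the indirect effect while the general rule attaches them to effect sizes. At 30 per arm this matters. Under the assumed paths, the sampling SD is of the same order as the effect (for example 0.074 against 0.06, and 0.124 against 0.20), and the chance of an estimate with the wrong sign runs from about 3% to 17%. These figures rest on the assumed *a* and *b*, no direct effect and complete data; larger true paths would make the sign more secure. No primary conclusion is affected unless the sentence is taken to cover the main CRT versus TAU effects, which is the less natural reading but one the wording does not exclude.

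**What to change.** Replace the closing sentence on mediation with: *Indirect effects will be reported with bootstrap 95% confidence intervals and without hypothesis tests or p-values.* Add a clause stating that this applies to the mediation analysis only, and that the CRT versus TAU effects at weeks 13 and 25 are reported with confidence intervals under the general rule.

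The cost is one reworded sentence and a few lines of code. No additional data are needed, since cognition and FAST are already scheduled at all three main assessments, and bootstrap resampling is already planned under Economic analyses.

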### Participants

Thirty participants will be assigned to the intervention arm (CRT with TAU) and 30 to the control arm (TAU alone); this sample size is recommended for pilot trials [14] to estimate efficacy by corroborating effect sizes for cognitive and functional outcomes. We anticipate recruiting approximately half of the sample from secondary/tertiary care and half from the community (approximately 15 from each recruitment strand per group). Community recruitment will comprise public advertisements using methods that have previously been successful [15]. Participants will be recruited if fully informed and willing to participate and if they meet the following inclusion criteria: aged 18–65, have a confirmed DSM-V diagnosis of bipolar I disorder (using the Mini International Neuropsychiatric Interview [16]), and be in a euthymic state at two time points 1 week apart, defined by scores of < 8 on the Hamilton Rating Scale for Depression and Young Mania Rating Scale (standardised cut-off scores for euthymia [17] on both occasions. No constraints exist based on sex or prior treatment, but fluency in English and the ability to use a computer are required (assessed verbally). Furthermore, we will exclude potential participants if they have evidence of a substantial neurological, neurodegenerative, substance-use or current diagnosis of personality disorder (assessed using standardised measures). Both women who are pre- and post-menopausal will be included; menopausal status and current phase of menstrual cycle at each assessment time point will be reported verbally and recorded. This will also be controlled for in analyses due to reliable findings of cognitive variations across the menstrual cycle [18].

Participants will be selected from services within South London and Maudsley NHS Trust (the national Affective Disorders Service and the OPTIMA Mood Disorders Programme), by identification of potentially eligible individuals through the Consent for Contact (C4C) SLaM initiative [19], which allows approved researchers access to a computerised retrieval system to rapidly screen limited, relevant case notes of consenting service users and by community advertisements and a research webpage.

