#### Randomisation

Following fully informed written consent, participants will be randomised to one of the two treatment arms (TAU or TAU + CRT). Randomisation is facilitated by the King’s College Clinical Trials Unit independent web-based system [20], holding the details needed for randomisation (treatment program, date of birth, and unique identity number). Trial participants will be randomised between the two parallel groups in a 1:1 allocation (30 participants per treatment group). A stratified block randomisation will allocate participants to treatment groups, with an equal number of participants in each stratification group (intensive-secondary or tertiary care; standard secondary care) using an initial random allocation sequence (n cases). All randomisation details will be locked following treatment allocation. The lead researcher (RS) will not be blinded to treatment allocation but the researcher conducting research assessments and trial statistician will be blind.

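### The mixed models are to be fitted by maximum likelihood for a missing-data reason that REML meets equally well; with at most 60 participants this makes the effect-size intervals slightly too narrow (minor)

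*Protocol article*

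**What the plan says.** The section on effect sizes for CRT versus TAU (objectives 1 and 2) describes one linear mixed model per outcome. On the data it states: "The linear mixed model will contain post-treatment measures of the outcome at the two follow-up time points, i.e. 13 and 25 weeks". The model has "fixed effects of trial arm, baseline measure of outcome, time and a time point by trial arm interaction" and a random effect for participant. On estimation it states: "With respect to missing data, linear mixed models will be estimated using maximum likelihood (ML"), and justifies this by valid inference when missingness is ignorable. REML and small-sample degrees of freedom are not mentioned. Baseline predictors of drop-out are to be added, with the caution that "given the small dataset the number of explanatory variables to be included will be necessarily small".

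On the use of the output, the Statistics section says "we will use largely descriptive statistics with inferential statistics used to generate respective confidence intervals and effect sizes". It lists three aims: trial feasibility, intervention feasibility, and intervention effect sizes (mean differences and standard deviations). It names feasibility parameters as the main purpose. On size, the Randomisation section states: "Trial participants will be randomised between the two parallel groups in a 1:1 allocation (30 participants per treatment group").

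**The concern.** ML estimates variance components as if the fixed-effect coefficients were known. The resulting downward bias is negligible in a large trial but not with 60 participants, and it grows with each added covariate and each drop-out. Standard errors and confidence intervals inherit it, in the same direction for every outcome modelled this way.

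The stated reason does not support the choice. Ignorability of missing data is a property of likelihood-based estimation using all observed outcomes, and REML shares it. The plan therefore accepts a known bias and gains nothing on missing data.

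At stake is the third aim. The Participants section ties the number recruited to this use: "this sample size is recommended for pilot trials [14] to estimate efficacy by corroborating effect sizes for cognitive and functional outcomes". Intervals that are too narrow overstate how well the pilot has pinned down those effects.

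**Working it through.** The article gives no standard deviation, drop-out rate, interval width or power figure, so there is no stated number to reproduce.

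**Inputs from the document**
- 60 participants, 30 per arm (Randomisation).
- Two outcomes per participant, weeks 13 and 25 (effect-size section).
- Five fixed-effect coefficients: intercept, arm, baseline, time, time by arm. Three are between-participant (intercept, arm, baseline) and two within-participant (time, time by arm).

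**Assumptions**
- Added between-participant covariates q = 0 to 3. The article says only that the number will be small. The Participants section also plans to control for menopausal status and menstrual phase, which would use up some of this allowance.
- Participants analysed n = 42 to 60.
- Correlation between the two visits, given the covariates, ρ = 0.7, with 0.5 as a check.

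**Closed form (complete pairs, compound symmetry)**

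The between-participant variance is proportional to 1 + ρ and the within-participant variance to 1 − ρ. ML shrinks them, relative to REML, by (n − p)/n and (n − 2)/n, where p = 3 + q. For the effect at one visit:

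variance ratio ML/REML = [(1 + ρ)(n − p)/n + (1 − ρ)(n − 2)/n] / 2

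The SE ratio r is its square root. Coverage is approximately the probability that a t variable with n − p degrees of freedom lies within ± r × (quantile used).

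- n = 60, q = 0: (1.7 × 57/60 + 0.3 × 58/60)/2 = (1.615 + 0.290)/2 = 0.9525; r = 0.976.
- n = 60, q = 3: (1.530 + 0.290)/2 = 0.910; r = 0.954.
- n = 48, q = 3: (1.4875 + 0.2875)/2 = 0.8875; r = 0.942.
- n = 42, q = 3: (1.4571 + 0.2857)/2 = 0.8714; r = 0.934.

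| n, q | SE shortfall | ML, z | ML, t | REML, z | Width of REML with t ÷ ML with z |
|---|---|---|---|---|---|
| 60, 0 | 2.4% | 93.9% | 94.4% | 94.5% | 1.047 |
| 60, 3 | 4.6% | 93.3% | 93.9% | 94.5% | 1.072 |
| 48, 3 | 5.8% | 92.8% | 93.6% | 94.3% | 1.093 |
| 42, 3 | 6.7% | 92.4% | 93.4% | 94.2% | 1.108 |

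With ρ = 0.5 the extremes barely change: r = 0.977 (n = 60, q = 0) and 0.939 (n = 42, q = 3).

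**Simulation of the planned model**

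There were 4,000 replicates per scenario, with 0 to 20% missing at week 13, 0 to 30% missing at week 25, q = 0, 1 or 3, and ρ = 0.5 or 0.7. SE ratios ran from 0.976 down to 0.940. Coverage was 92.7 to 94.0% for ML with z, 93.5 to 94.7% for ML with t, and 94.5 to 95.5% for REML with t. Monte Carlo error on a coverage near 93% is about ±0.8 points (1.96 × √(0.93 × 0.07/4000)). The simulation therefore confirms direction and rough size but does not rank neighbouring scenarios.

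**The case against.** The strongest reply is that this is too small to matter in a pilot that sets no significance threshold. For the model as written, with all 60 observed and nothing added, the standard error is 2.4% too small. The sampling error of an SD from about 60 people is roughly 9% (1/√(2 × 59)), well above that bias. This stands as an argument about severity. It does not remove the error, which is systematic and avoidable.

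The second reply is that part of the shortfall depends on the quantile. With 60 complete and no added covariates, ML with z loses 1.1 points, ML with t 0.6, and REML with z 0.5. About half of the loss therefore comes from assuming z. The article does not state a quantile, and an analysis plan may properly supply one. This also stands. The part due to ML remains, because the article states that choice outright.

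Four stronger readings are tempting, and the document does not support them.
- A reader might infer that the pilot's main output is compromised. The Statistics section makes feasibility parameters the main purpose, and those are descriptive rates that do not come from the mixed models.
- A reader might infer that the SDs for the next trial's sample size will be too low. The article promises standard deviations but does not say they are model-based, and ordinary sample SDs are unaffected.
- A reader might obtain a larger loss by assuming many added covariates. The section itself says there will be few.
- In the other direction, a reader might take the sentence saying inferential statistics will not be reported as removing treatment-effect intervals altogether. It follows the mediation sentence and does not clearly reach the treatment effects, whereas the Statistics section promises "inferential statistics used to generate respective confidence intervals and effect sizes".

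**Conclusion.** The point holds as a minor one. ML is a stated choice whose only given reason applies equally to REML. Over the assumed range (42 to 60 analysed, 0 to 3 added covariates, ρ about 0.7), it understates the variance of the treatment-effect estimates by about 5 to 13% and the standard error by about 2 to 7%. Coverage of nominal 95% intervals falls to about 92.4 to 93.9% with z, or 93.4 to 94.4% with t (93.6% at the lower end if at least 48 are analysed). Under-coverage with t quantiles shows that the shortfall is not only a matter of z versus t. Effect point estimates are essentially unchanged. Planning SDs are affected only if they are taken from the fitted model. The numbers analysed, the covariate count and the correlation are assumptions, since the article gives none of them.

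**What to change.** In the effect-size section, replace maximum likelihood with restricted maximum likelihood and name Kenward-Roger or Satterthwaite degrees of freedom for the intervals. Leave the missing-at-random statement as it is. Add that any model-based SD carried to the larger trial comes from the REML fit.

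This changes one phrase, adds one sentence and needs no new data. Standard errors rise by about 2.5 to 7% relative to ML (1/0.976 to 1/0.934). Intervals become about 5 to 11% wider than ML with z, and simulated coverage returns to about 95%.
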